## Abstract

**Background:**

The ε4 allele of the Apolipoprotein E gene (APOE-ε4) is a potent genetic risk factor for sporadic Alzheimer’s disease (AD). Amnestic mild cognitive impairment (aMCI) is an intermediate state between normal cognitive aging and dementia, which is easy to convert to AD dementia. It is an urgent problem in the field of cognitive neuroscience to reveal the conversion of aMCI-ε4 to AD. Based on our preliminary work, we will study the neuroimaging features in the special group of aMCI-ε4 with multi-modality magnetic resonance imaging (structural MRI, resting state-fMRI and diffusion tensor imaging) longitudinally.

**Methods/Design:**

In this study, 200 right-handed subjects who are diagnosed as aMCI with APOE-ε4 will be recruited at the memory clinic of the Neurology Department, XuanWu Hospital, Capital Medical University, Beijing, China. All subjects will undergo the neuroimaging and neuropsychological evaluation at a 1 year-interval for 3 years. The primary outcome measures are 1) Microstructural alterations revealed with multimodal MRI scans including structure MRI (sMRI), resting state functional MRI (rs-fMRI), diffusion tensor imaging (DTI); 2) neuropsychological evaluation, including the World Health Organization-University of California-LosAngeles Auditory Verbal Learning Test (WHO-UCLA AVLT), Addenbrook’s cognitive examination-revised (ACE-R), mini-mental state examination (MMSE), Montreal Cognitive Assessment (MoCA), Clinical Dementia Rating scale (CDR).

**Discussion:**

This study is to find out the neuroimaging biomarker and the changing laws of the marker during the progress of aMCI-ε4 to AD, and the final purpose is to provide scientific evidence for new prevention, diagnosis and treatment of AD.

**Trial Registration:**

This study has been registered to ClinicalTrials.gov (NCT02225964, https://www.clinicaltrials.gov/) in August 24, 2014.

## Background

Alzheimer’s disease (AD) is a common neurodegenerative disorder, which is increasingly prevalent among the elderly. AD patients usually complain of memory impairment and serious decline of the daily living abilities. The aMCI is an intermediate state between normal cognitive aging and dementia, which is easily progressed to AD dementia. Thus, the effective therapy of AD is to be delivered once the diagnosis is made at the very early stages of AD, ideally in the phase of aMCI. The human apolipoprotein E (APOE) gene has three polymorphic alleles (E2, E3, and E4) [1]. APOE-ε4 was confirmed to be related with sporadic AD risks by increasing the risk of developing AD and reducing the age of onset [2]. Therefore, it is an urgent requirement in the field of cognitive neuroscience to reveal the underlying neurological mechanism of the conversion of aMCI to AD in the patients with APOE-ε4.

Although the cognition evaluation is simple, the accuracy of the diagnosis depends on the professional skills of the doctor and the collaboration of patients. On the other hand, MRI might be a promising strategy for early diagnosis of AD [3]. MRI might be the best diagnosis method for AD by mapping both structures and functions of the human brain. Structurally, studies showed that brain atrophy in AD patients first appears in the medial temporal lobe (MTL), and then involves the parietal lobe, frontal lobe and occipital lobe, and finally the anterior cingulate cortex [4, 5]. Consistent with these findings, evidence from our team has demonstrated the progressive alterations of brain structures during the progression to AD [6]. Compared with APOE-ε4 non-carriers, the carriers exhibited greater medial temporal lobe atrophy [7]. APOE-ε4 is an independent risk factor for the hypotrophy hippocampus in patients with AD and MCI [8]. Decreased gray matter volume mainly restricts in the right brain area for aMCI-ε4 patients [9]. Not the degree of atrophy, but the rate of atrophy in a certain region of brain demonstrate close relationship with the AD progression [10]. The rate of hippocampal atrophy is suggested to be an early marker of incipient memory decline and dementia [11]. The longitudinal study indicated that rate of volumetric loss was significantly greater among MCI-ε4 compared with non-carriers [12]. Compared with structural MRI, diffusion tensor imaging (DTI) is a more sensitive method for detecting white matter damage [13]. A short-term follow-up study showed that AD patients had lower fractional anisotropy (FA) than controls in the fornix and anterior portion of the cingulum bundle, and these FA values were positively correlated with cognitive score [14]. The APOE-ɛ4 modulates white matter (WM) before clinical manifestations and cognitive impairment [15]. The changes of white matter is accompanied with the cognitive function decline in APOE-ε4 carriers [16]. Previous studies suggested that rs-fMRI is a potential functional biomarker for cognitive impairment. The aMCI subjects showed that posterior cingulate cortex/precuneus (PCC/PCu) hyper-functional connectivity was found at baseline, while a substantial decrease of these connections was observed at follow-up [17]. Our team observed that the aMCI patients had decreased amplitude of low-frequency fluctuations (ALFF) values in the PCC/PCu, anterior medial prefrontal cortex (aMPFC), hippocampus/parahippocampal gyrus (PHG), basal ganglia, and prefrontal regions, and increased ALFF values mainly in several occipital and temporal regions [18]. APOE-ε4 exerts an influence on brain function in patients with MCI. Using whole-brain pulsed arterial spin labeling (ASL) magnetic resonance imaging suggest that cognitive status and APOE genotype have interactive effects on cerebral blood flow (CBF) [19]. MCI-ε4 patients demonstrated significantly increased CBF [20]. However, deficits exist in these studies that using rs-fMRI to reveal the effect of APOE-ε4 on MCI patients.

For the purpose of early diagnosis, the researchers have been focusing on the aMCI window. Although previous studies provide important information for the conversion of aMCI to AD, they were based on the single modality neuroimaging analysis. Moreover, previous studies ignored one of the major factors that affects the course of the MCI converting to AD is the APOE-ε4. Thus, the purpose of the current trial is to longitudinally investigate the multi-modal (structural MRI, resting state-fMRI and diffusion tensor imaging) neuroimaging characteristics of aMCI-ε4 patients. We hope to provide scientific evidence for more effective prevention, diagnosis and treatment of AD.

## Methods/Design

The scheme of the current prospective trial is described in Fig. 1.

**Fig 1 Fig1:**
[figure not shown]
Flowchart of the current prospective diagnostic trial

### Subject

Subjects inclusion: subjects with aMCI included the following: (1) memory complaint, preferably confirmed by an informant; (2) a single domain or multi domain cognitive decline; abnormal objective memory impairment documented by the scores falling 1.5 SD below the age and education matched-specific norms on memory test; being free from dementia according to the Diagnostic and Statistical Manual of Mental Disorders, Fourth Edition, revised (DSM-IV-R); (3) objective memory impairment, cutoff points of MiniMental State Examination (MMSE) score: 19 (no formal education), 22 (1 to 6 years of education), and 26 (7 or more years of education); cutoff points of Montreal Cognitive Assessment (MoCA): 13 (no formal education), 19 (1 to 6 years of education), and 24 (7 or more years of education) [21]; a Clinical Dementia Rating (CDR) score of 0.5; (4) the Han nationality, right-handed (the Edinburgh handedness scale score >40 points); no fixed dentures and can accept MRI scan; (5) able to complete 3 years follow-up.Subjects exclusion: (1) those who have a clear history of stroke; (2) severe depression that led to mild cognitive impairment (Hamilton Depression Rating Scale score ≥ 24 points); (3) other nervous system diseases, which can cause cognitive impairment (such as brain tumors, Parkinson's disease, encephalitis, and epilepsy); (4) cognitive impairment caused by traumatic brain injury; (5) other systemic diseases, which can cause cognitive impairment, such as thyroid dysfunction, severe anemia, syphilis, and HIV; (6) a history of psychosis or congenital mental growth retardation; and (7) subjects with contraindications for MRI.

### Neuropsychological assessments

All subjects will receive a standardized clinical and neuropsychological evaluation, including WHO-UCLA AVLT, ACE-R, MMSE, MoCA, CDR.

### APOE genotype

After the neuropsychological assessments and before the MRI scan, genomic DNA will be extracted from peripheral blood using a Blood Genomic DNA Extraction Kit. The APOE genotypes will be determined by a restriction enzyme polymerase chain reaction technique. Only subjects carrying the gene of E3/E4 or E4/E4 will be enrolled in this study group.

### Magnetic resonance brain imaging

#### Imaging protocol

Imaging data will be acquired using a 3.0 T Trio Siemens scanner at XuanWu Hospital, Capital Medical University. For each participant, conventional brain T1-weighted (T1WI), T2-weighted (T2WI) and fluid-attenuated inversion recovery (FLAIR) images will be obtained to exclude serious brain diseases. Brain MR images will be inspected by an experienced neuroradiologist (with over 5-year experience).

sMRI. using a sagittal MP-RAGE sequence with the following imaging parameters: TR = 1900 ms; TE = 2.2 ms; inversion time = 900 ms; flip angle = 9^。^; FOV = 256 mm × 256 mm; matrix = 256 × 256;176 slices, thickness = 1.0 mm.

rs-fMRI. using an echo-planar imaging sequence with the following parameters: repetition time (TR) = 2000 ms, echo time (TE) = 40 ms, flip angle (FA) = 90∘, number of slices = 28, slice thickness = 4 mm, gap = 1 mm, voxel size = 4 × 4 × 4 mm^3^, and matrix = 64 × 64. Participants will be asked to lie quietly in the scanner with their eyes closed during data acquisition. Each scan lasted for 478 s.

DTI. using an echo planar imaging (EPI) sequence in 32 independent, non-collinear directions of a b-value = 1000 s/mm^2^, and one additional image with no diffusion weighting (b = 0). TR = 11000 ms, TE = 98 ms, flip angle = 90^。^, field of view (FOV) = 256 mm × 256 mm, imaging matrix = 128 × 128, number of slices = 60, and slice thickness = 2 mm. Three acquisitions will be averaged to increase the signal-to-noise ratio.

#### MRI image analysis

sMRI data analysis. Voxel-based morphometry (VBM) with DARTEL will be used to characterize gray matter volume (GMV). Voxel-based morphometry with DARTEL will be performed using SPM8 (Welcome Trust Center for Neuroimaging, London, UK, http://www.filion.ucl.ac.uk/spm/software/spm8/). For the analysis of cortical thickness, we will use the software package of the Montreal Neurological Institute (MNI)(http://wiki.bic.mni.mcgill.ca/index.php/CIVET). This process includes structural image non-uniformity correction, spatial standardization, tissue segmentation (gray matter, white matter and cerebrospinal fluid), internal and external surface extraction of gray matter as well as the definition and measurement of cortical thickness.

rs-fMRI data analysis. Image preprocessing will be performed by using SPM8 (http://www.fil.ion.ucl.ac.uk/spm/) and Data Processing Assistant for Resting-State fMRI. The preprocessing procedures will be performed including removal of the first 10 volumes, slice timing, and head motion correction. All rs-fMRI data will be satisfied the criteria of spatial movement in any direction < 3 mm or 3^o^ and the subjects will be demonstrated no significant group differences in the head motion parameters (i.e, three translation and three rotation parameters). To normalize the fMRI data spatially, the T1-weighted images will be firstly registered to the mean functional data, and the resulting aligned T1 data set will be segmented and transformed into MNI space using the DARTEL toolbox, and a group template will be generated. Next, the motion-corrected functional volumes will be specially normalized to the group template using the transfer parameter estimated by DARTEL segmentation and resampled to 3 mm isotropic voxels. Further, the functional images will be spatially smoothed with a 4 mm Gaussian kernel. The linear detrend and temporal bandpass filtering (0.01 – 0.08 Hz) will be performed to reduce the influences of low-frequency drift and high-frequency physiological noise. Finally, several nuisance signals will be regressed out from the data, including the six motion parameters, the global, the white matter, and the cerebrospinal fluid signals.

Functional connectivity (FC) analysis using DPARSF software (http://www.restfmri.net/forum/DPARSF).

DTI data analysis. DTI data processing will be carried out using FSL software (FMRIB Software Library, http://www.fmrib.ox.ac.uk/fsl). Initially, eddy current correction will be run to correct gradient-coil distortions and small-head motions using affine registration to a reference image (b0 volume). The brain voxels of DTI data will be extracted using the Brain Extraction Tool (BET). The maps of diffusion tensor parameters including FA and MD will be calculated using DTI-FIT tool, which fits a diffusion tensor model to diffusion-weighted images for each voxel. Voxel-wise statistical analysis of the FA and MD data will be performed for regional differences using TBSS.

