### Follow up

All aMCI-ε4 patients will undergo a follow-up review of approximately 3 years with 1-year interval. They will get the entire clinical examination, neuropsychological assessment and MRI scan during the baseline period. Individuals will come back to the XuanWu Hospital once 1 year for countercheck. All the evaluations are the same as that they receive during the first clinic visit. According to the diagnosis in the follow-up stage, aMCI-ε4 patients will be divided into converters and nonconverters to AD.

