### Sample size calculation and statistics

A total of 1000 right-handed aMCI patients will be recruited in this study. aMCI-ε4 patients is about 26.6 %, and annual conversion rate of aMCI-ε4 patients convert is 15.9 % [22]. Thus, we plan to recruit 200 patients with aMCI-ε4. There will be about 90 aMCI-ε4 converted into AD after 3 years of follow-up.

Demographics and clinical characteristics of the subjects will be analyzed using SPSS 17.0. Two-sample two-tail *t* test or two-tail Pearson chi-square test will be used to explore differences of these data among two groups (converters and nonconverters). *P* < 0.05 is considered as with statistical significance.

For images analysis. To determine the difference between two groups (converters and nonconverters), we will perform a two-sample *t*-test. The significant level will be set at *P* < 0.05.

To determine the difference between intra-groups, we will perform a One-way analysis of variance (ANOVA). Further, Dunnett-*t* test will be performed for differences among intra-groups. The statistical threshold of the two test will both be set at *P* <0.05.

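### The rs-fMRI section makes a non-significant group difference in head motion a condition on the data; this does not show balance, cannot be guaranteed, and if it fails can be met only by changing who is analysed

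*Protocol article*

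**What the plan says.** The rs-fMRI paragraph of the protocol article (MRI image analysis) places two conditions on the data in one sentence. The first is a limit on each scan, "spatial movement in any direction < 3 mm" or 3 degrees. The second is that "the subjects will be demonstrated no significant group differences in the head motion parameters", and the parameters are listed as "three translation and three rotation parameters". No step is given for the case where a difference is found, and no margin says how small a difference counts as balanced.

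The same paragraph also provides a motion correction within each scan: "several nuisance signals will be regressed out from the data, including the six motion parameters", together with the global, white-matter and cerebrospinal-fluid signals.

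That sentence does not name the groups. They are read here from two other sections. Under Follow up, "aMCI-ε4 patients will be divided into converters and nonconverters to AD" on the basis of the follow-up diagnosis. Under Sample size calculation and statistics, "To determine the difference between two groups (converters and nonconverters), we will perform a two-sample *t*-test", at a 0.05 level and with no covariate.

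**The concern.** The per-scan limit is a rule that can be applied to any scan without knowing the patient's outcome. The second condition is different in kind: it states in advance what the data will show about two groups that exist only once the outcome is known. Three problems follow.

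- If the tests are non-significant, the condition counts motion as balanced, although a non-significant test is compatible with a real difference.
- If the groups are in truth alike, one of six tests may still be significant by chance, and the article does not say what happens then.
- If a difference appears, then with the parameters and the test held fixed, the condition can be met only by changing the set of patients analysed after conversion status is known.

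At stake is one of the three imaging modalities named in the primary outcome. The stated aim is to describe how an imaging marker changes as aMCI-ε4 progresses to AD. If converters move more, dropping those with the most motion could take out the patients most informative about that course, and a motion difference that passes the check could show up in part as a connectivity difference.

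**Working it through.** **Inputs from the article.** "Thus, we plan to recruit 200 patients with aMCI-ε4"; "There will be about 90 aMCI-ε4 converted into AD after 3 years of follow-up"; annual conversion rate 15.9 %; six motion parameters; image comparisons at P < 0.05.

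**Assumptions.** The article gives no test or level for the motion check, so a two-sided two-sample test at 0.05 is assumed for each parameter. All 200 patients are taken to have usable scans. The article has no motion data, so the true differences (0.1 to 0.5 SD) are assumed values.

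**Step 1, group sizes.** The stated 90 converters is not reproduced from the stated rate:
- compounding: 200 × (1 − 0.841³) = 81.0
- simple addition: 200 × 3 × 0.159 = 95.4
- constant hazard: 200 × (1 − exp(−3 × 0.159)) = 75.9

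That gap is a separate matter. Both 90 v 110 (as stated) and 81 v 119 (compounding) are carried forward.

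**Step 2, what passes as non-significant.** The standard error of a standardised difference is √(1/n₁ + 1/n₂).
- 81 v 119: √(1/81 + 1/119) = 0.144. With t(0.975, 198) = 1.972, any observed difference up to 1.972 × 0.144 = 0.284 SD in a parameter is non-significant.
- 90 v 110: √(1/90 + 1/110) = 0.142, giving 1.972 × 0.142 = 0.280 SD.

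**Step 3, how often a true difference is missed.** Power is approximately Φ(d/SE − 1.96). For d = 0.30 at 90 v 110: 0.30/0.1421 = 2.11, and Φ(0.15) = 0.56, so 44 % are missed.

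| True difference (assumed) | Missed, one parameter, 90 v 110 | Missed, one parameter, 81 v 119 | Missed in all six if each is shifted and independent, 90 v 110 |
|---|---|---|---|
| 0.1 SD | 90 % | 90 % | 52 % |
| 0.2 SD | 71 % | 72 % | 13 % |
| 0.3 SD | 44 % | 45 % | 0.7 % |
| 0.4 SD | 20 % | 21 % | < 0.1 % |
| 0.5 SD | 6 % | 6.5 % | < 0.1 % |

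The last column is the single-parameter figure to the sixth power, for example 0.71⁶ = 0.13. The per-parameter figures apply to a difference in one parameter only. A shift shared by all six is much less likely to pass unnoticed.

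**Step 4, failure by chance.** With no true difference and six independent tests, the chance of at least one significant result is 1 − 0.95⁶ = 0.265. Were the six perfectly correlated, it would be 5 %.

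**Step 5, what enforcing the condition could cost.** This is an illustration only. One normal motion parameter was simulated at 90 v 110 (1,500 runs), and the converter with the most motion was dropped repeatedly until p ≥ 0.05. Where the first test was significant, the mean number dropped was 4.7, 6.4, 9.1 and 13.1 of 90 for true differences of 0.2, 0.3, 0.4 and 0.5 SD. Averaged over all runs, a difference of 0.17, 0.22, 0.25 and 0.26 SD remained. This way of meeting the condition loses converters and still does not balance the groups.

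**The case against.** The strongest reply is that the sentence is a clumsily worded balance check and not a gate. The only exclusion criterion actually written down is the movement limit, which does not depend on conversion status. A team that found a difference could simply report it or adjust for it. A reader might infer that the plan intends to remove scans by outcome; the article does not say so. What stands against the reply is that the sentence, taken as written, is a condition on the data, and it offers no alternative if the condition is not met.

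A reader might also infer that motion is left uncorrected. That is wrong: images are motion-corrected and the six parameters are regressed out of each scan. This reduces the effect of motion on each patient's signal. It does not put a motion term in the comparison between patients, and the article does not present it as a replacement for the group condition.

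It is fair to say that the harm is conditional. Nothing in the article shows that converters move more, and if the groups do not differ, the condition may be met with no biased exclusion. It is also fair to say that a motion covariate and motion tables could sit in a fuller protocol or SAP that is not shown. Their absence from the article is therefore not the point. The point is the condition that the article does state.

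**Conclusion.** The point holds in a limited form. The article fixes a data result as a condition, for groups that are defined by the outcome. Meeting it shows little about balance in any single parameter: a true 0.30 SD difference is missed 44 to 45 % of the time, whichever converter count is used. It can also fail by chance, with up to a 26.5 % probability if the six tests are independent. These figures rest on an assumed two-sided 0.05 test per parameter, usable scans from all 200 patients, and assumed SD differences. The reading of the groups as converters and nonconverters comes from the Follow up and statistics sections.

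The stronger conclusion that the rs-fMRI contrast is biased whichever way the check falls is not supported. Bias is possible if converters move more and scans are dropped to meet the condition, or if residual motion effects survive the within-scan regression. Neither is established. This is a cheap improvement worth making before conversion status is used in the analysis.

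**What to change.** - Delete the requirement of no significant group difference in head motion.
- State that the existing limit of 3 mm or 3 degrees is the only motion-based exclusion, applied blind to conversion status at every visit.
- Include a per-scan motion summary, for example mean framewise displacement, as a covariate in the rs-fMRI comparison of converters with nonconverters, and give the unadjusted result as a sensitivity analysis.
- Report motion and the number of excluded scans by group.

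The cost is a change of wording and one degree of freedom, because the summary comes from realignment parameters that the preprocessing already produces. The drawback is that adjustment may attenuate a real difference if motion is itself a sign of progression. The unadjusted sensitivity analysis lets the reader see how much the result depends on it.

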### Follow up

All aMCI-ε4 patients will undergo a follow-up review of approximately 3 years with 1-year interval. They will get the entire clinical examination, neuropsychological assessment and MRI scan during the baseline period. Individuals will come back to the XuanWu Hospital once 1 year for countercheck. All the evaluations are the same as that they receive during the first clinic visit. According to the diagnosis in the follow-up stage, aMCI-ε4 patients will be divided into converters and nonconverters to AD.

